#### Pittsburgh Sleep Quality Index questionnaire (PSQI)

Given that actigraphy distinguishes wakefulness from sleep based on movements and that there is a possibility that a person with poor sleep quality may stay awake while lying still, the Pittsburgh Sleep Quality Index questionnaire will be used. The PSQI is the most commonly used measure for subjective self-report sleep quality. In a study that examined test-retest reliability in a sample of 76 individuals with insomnia over a period of 2 days to several weeks, the PSQI showed a correlation of 0.87 for global score (34). This 24-item questionnaire captures “overall” subjective sleep quality and will be used before and after each intervention. This instrument gives an accumulative score based on seven subcomponents: subjective sleep quality, sleep latency, sleep duration, habitual sleep efficiency, sleep disturbances, use of sleeping medication, and daytime dysfunction (35). The total score ranges from 0 (good sleep quality) to 21 (poor sleep quality) with a 0–3 scoring range for each of the seven subcomponents (35). To assess significance, baseline scores will be compared to music alone, BBFs alone, and music with BBF.

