#### Philips Actiwatch Spectrum Pro actigraphy monitor

Since this study will not be conducted within a sleep laboratory using polysomnography, the Philips Actiwatch Spectrum Pro monitor will be used for home use. This clinical grade tri-axial accelerometer-based wearable device works by measuring movement of the body. Using special software, that information is then articulated into a graphical and tabulated report that shows the movement that occurred throughout the wake and sleep cycles. The report gives the: (1) time the participant went to bed, (2) time awaken, (3) number of hours in bed, (4) total number of hours asleep, (5) number of minutes it took to fall asleep, (6) sleep efficiency percentage, (7) number of minutes awaken after sleep onset, and (8) total number of times awaken after falling asleep. Measures will be collected during all phases. All phases will be analyzed to assess the trends and any statistical differences across time. The device also measures level and type of light exposure in the event the investigator wants to assess if light exposure played a role in the analysis given that some of the participants may work varying shifts (e.g., sleeping at night vs. sleeping during the day) (36). In a 2020 systematic review assessing the utility of sleep actigraphy, the Actiwatch was one of the most used devices with one third of the 34 studies reviewed reporting high participant compliance and low rate of device malfunction (4–6.7%) (37).

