### Outcomes measures

The primary aim of this study is to assess if an audio program that has theta and delta BBFs arranged in an order that mimics a healthy adult hypnogram will improve sleep quality. To subjectively measure improvement in sleep quality, the PSQI total scores from Interventions 1 and 2 will be compared to baseline to note any statistically significant differences. This score will also be correlated with the sleep efficiency percentage scores taken from the sleep actigraphy monitor as a secondary validation. To objectively measure improvement in sleep quality, sleep efficiency percentage calculated from the sleep actigraphy monitor will be used. Even though 80 to 85% is considered good sleep efficiency, improvement in sleep efficiency will be determined by identifying any statistically significant changes when compared to the participant's baseline where there was no intervention. Sub measures of sleep efficiency such as sleep latency, number of minutes awake after sleep onset, and number of times awaken throughout the night will be analyzed individually. Data collected from the National Sleep Foundation Sleep Diary will be assessed to see if there are any relationships between exercise, medication use, napping, sleepiness during the day, mood, alcohol, food and caffeine intake, timing of caffeine intake, and bedtime routine and the various sleep outcomes. The Post-Study Questionnaire will be used for informational purposes to assess the participants' experience, perception of the technology, and the feasibility of conducting Phases 3 and 4.

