Based on the findings of the primary aim, the secondary aim of this study is to map out a plan for a series of feasibility studies to support the development of a customizable all-night audio track to induce sleep, sustain sleep and to provide a structure waking. First, if Phase 2 shows that the theta/delta combination with appropriate breaks for REM and timing did not sync appropriately due to each participants' unique sleep cycles, this step will be repeated using theta BBF only as theta will allow participants to fall back to sleep in the event they have a longer sleep latency or if awaken throughout the night. If Phase 2 shows efficacy with using the theta/delta combination, Phase 3 will next incorporate theta, alpha and beta BBFs, respectively, at the end of a 6-, 7-, or 8-h audio track to assess if it can trigger a structured waking process. For this phase the attention will be focus more on the ending of sleep such as awakening time and feeling upon awakening. In this case it may not be necessary to use BBFs for the entire night but to simply add a structured waking protocol near the end of an audio track. If Phase 3 proves successful, Phase 4 will combine lessons learned from Phases 1, 2, and 3 to create a customized all-night audio track starting with alpha and theta BBFs, that will transition to intermitted halting of theta and delta BBFs, and end with theta, alpha and beta BBFs. The ideal participant for this study would be persons with insomnia with the hope of using this technique later for persons with sleep phase disorder, non-24-h circadian rhythm disorder, irregular sleep wake disorder, shift work disorder, and/or jet lag disorder. Given that close assessment of sleep stages will be imperative to determine if the brainwaves are in fact being entrained, this study would be conducted within a sleep lab. According to Jirakittayakorn and Wongsawat (29), it may be possible to use electroencephalograms, electro-oculogram, and electromyograms without full polysomnography as they are sufficient for scoring sleep stages and offer better comfort for participants. Although this will be time consuming, equipment intensive, and would require much from the participant, a substantially smaller sample size may be adequate if data from the previous phases were found to be significant. If sleep actigraphy data from the previous phases proved to be consistent and reliable, Phase 4 could also include a hybrid approach of using actigraphy for 1 week and polysomnography later to truly assess if entrainment is taking place.

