
### Limitations

The use of polysomnography is the gold standard for assessing sleep. However, when multiple data collection points are needed on an intervention that has not been well-studied, it is best to start by conducting assessments with low participant burden, low risk, low cost, and user-friendly and relevant data collection tools. Using a model hypnogram to construct a BBF algorithm may not work for everyone given that each person has their own sleep cycle rhythm, and that age and gender can play a role. However, if changes are noted in sleep parameters such as sleep latency, wake upon sleep onset, or number of times awakened this may provide evidence that the brainwaves can in fact be entrained. Finally, constructing an audio file that allows breaks for REM is a difficult task as sleep cycles are individualized. Using the 90–110-min mark to halt BBF to provide a break is the best educated option aside from simply using continuous theta BBF for the entire night.

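### The mistiming branch of the plan for later phases cannot be decided from Phase 2 data, and its efficacy branch uses a baseline comparison that music alone could satisfy

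*Protocol article*

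**What the plan says.** All references are to the protocol article.

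- **Rule, mistiming branch** (Outcomes measures): if Phase 2 shows that the theta/delta audio "did not sync appropriately due to each participants' unique sleep cycles, this step will be repeated using theta BBF only".
- **Rule, efficacy branch** (same section): "If Phase 2 shows efficacy with using the theta/delta combination, Phase 3 will next incorporate theta, alpha and beta BBFs".
- **Criterion for improvement** (same section): in actigraphic sleep efficiency, "any statistically significant changes when compared to the participant's baseline where there was no intervention". The Aims section is wider and asks for improvement against a control group as well as against no intervention.
- **Instrument** (PSQI section): "actigraphy distinguishes wakefulness from sleep based on movements".
- **Judging entrainment** (Outcomes measures, on Phase 4): "close assessment of sleep stages will be imperative to determine if the brainwaves are in fact being entrained".
- **Inference from actigraphy** (Limitations): if latency, wake after onset or number of awakenings changes, "this may provide evidence that the brainwaves can in fact be entrained".

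**The concern.** The two branches rest on different kinds of condition. Efficacy is an outcome that the trial measures. Failure to sync is a statement about cause: the audio was out of step with the sleeper's own cycles, and that is why it did not work. To show this, Phase 2 would have to observe the cycles, or their alignment with the audio, and it observes neither.

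A null Phase 2 therefore leaves the mistiming explanation available without any data that could contradict it. In the other direction, a change from the no-intervention baseline could count as efficacy, or be read as a sign of entrainment, although music or expectation could have produced it. What is at stake is the secondary aim, the choice of the next study, and how Phase 2 is interpreted.

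**Working it through.** The plan gives no figure for this rule, so the check sets the condition of each branch beside what is collected, with one short calculation.

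**1. What Phase 2 records** (instrument sections and Table 2)

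- Actigraphy: eight outputs, namely bed time, wake time, hours in bed, hours asleep, minutes to fall asleep, sleep efficiency, minutes awake after onset and number of awakenings. The device also records light. None of these is a sleep stage, a REM time or a cycle length.
- PSQI: seven self-reported components, none of them a stage.
- Sleep diary: the on-waking questions are not used; the eight bedtime items cover daytime habits and state.
- Post-study questionnaire: experience, adherence, comfort and perceived allocation.
- Audio: the participant presses play at bedtime and the file loops (Weeks 3 and 4). No playback log is described.

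So the mistiming condition has no measured counterpart. The article's own account of Phase 4 agrees: staging is needed to judge entrainment, and polysomnography is named as the means to assess it properly.

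**2. Can the efficacy test separate the two explanations?**

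Input: two-sided α = 0.05 (Power analysis and data analysis plan). Consider a test of BBF against music.

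- BBF has no effect: net effect 0, so P(non-significant) = 1 − 0.05 = 0.95.
- BBF could work but is mistimed so that nothing is gained: net effect 0, so P(non-significant) = 0.95.
- Likelihood ratio = 0.95 / 0.95 = 1.

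A null result does not favour either explanation. A third source is chance. The Cohort 1 calculation uses power 0.85, so a real effect of the size assumed there would still be missed with probability 1 − 0.85 = 0.15. That null could be labelled a sync failure too.

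**3. Can the efficacy branch be met without BBF?**

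- The criterion in Outcomes measures is a significant change from the no-intervention baseline.
- Study design says that earlier studies found music alone to help sleep. It also reports that in Phase 1, where both groups heard music, 80% of participants felt they fell asleep faster, whichever group they were in.
- A period of music with BBF could therefore beat baseline with no contribution from BBF. The Aims section would exclude this through its control group; the criterion as worded in Outcomes measures would not.

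**4. Does the Limitations sentence fill the gap?**

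No. It runs only from an observed change to possible entrainment. It gives no way to show that an absent effect was due to timing.

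**The case against.** The strongest reply is that this is a condensed article, that the secondary aim is a planning exercise and not an estimand, and that the limits of actigraphy are disclosed. Several parts of that reply stand, and they rule out stronger readings that a reader might be tempted to make.

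- *The secondary aim cannot be met at all.* Not supported. The efficacy branch has a stated criterion; only the mistiming branch is undecidable.
- *A plain negative result has no route.* The text gives none, but the Aims section refers the phase plan to Figure 3, which is not shown. A route may exist there.
- *Every null will be declared a timing failure.* The article does not say so. It says only what follows if Phase 2 shows non-sync. The problem is that Phase 2 cannot show it.
- *Music effects are uncontrolled.* Not so. Both cohorts include a music-alone period, blinded in Cohort 2, and the Aims section names a control group. The weakness is that the criterion in Outcomes measures does not use them.
- *The article claims proof of entrainment.* The Limitations sentence is hedged, and deferring staging to Phase 4 is a declared stepwise choice.
- *A 30-minute latency puts the audio out of step by 30/90 = 0.33 of a cycle, unseen.* Latency is recorded. The figure of under 30 minutes is a listed sleep parameter, not an entry limit. The file opens without BBF for a length not given. The ratio is only illustrative.

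The main point remains. A stated rule needs a finding that the collected data cannot supply, and the article itself says what would supply it. That is a conflict in the text, not detail left to a fuller document.

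**Conclusion.** The concern holds for the mistiming branch. Phase 2 cannot decide it, because sleep stage and cycle timing are not measured, and a null from mistiming looks the same as a null from no effect (likelihood ratio 1). This assumes that mistiming brings the net effect to about zero; a partly mistimed audio with a smaller effect would still not be identified as mistimed. The efficacy branch is decidable, but as worded in Outcomes measures it could be met by music alone and does not match the control-group comparison in the Aims section.

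The effect is limited to the secondary aim and to interpretation. The primary analysis, type I error and sample size are not touched. It should be corrected, because the change is in wording and the choice of the next study depends on it.

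**What to change.** Reconcile Aims, Outcomes measures and Limitations as follows.

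1. For planning later phases, base efficacy on the randomised within-person comparisons of BBF with music in sleep efficiency. The blinded Cohort 2 comparison (music with BBF against music) is the main evidence; the Cohort 1 comparison (BBF alone against music) supports it.
2. State that a null comparison is reported as no effect shown, and that Phase 2 cannot attribute it to timing.
3. In Limitations, confine the inference to differences between BBF and music conditions, described as effects on sleep parameters and not as evidence of entrainment.
4. Do not replace the mistiming branch with a subgroup or interaction rule on actigraphic latency: baseline latency does not measure sync, and power would be low.

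Which audio or phase follows each result is for the investigators.

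**Cost.** No new data are needed. The planned crossover mixed model already has intervention, period and sequence as fixed effects, so the comparisons come from it. Fewer results would support continuing. Cohort 2 was sized for a different question (similarity of BBF alone and music with BBF), so its power for the comparison with music is not stated; a null there should be read with its confidence interval.

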
## Discussion

As evidence of the many studies that have been conducted and the increase interest in BBFs, there is enough evidence to support the possibility of using BBFs to entrain a full night of sleep. Although polysomnography is the gold standard for assessing sleep stages and sleep quality, conducting small feasibility studies will provide valuable information for a more comprehensive study as each phase builds on its predecessor. Studying the three transition points of sleep (e.g., falling asleep, staying asleep, and awakening) individually instead of assessing an entire night of sleep provides more data for customization especially if using the same participants in subsequent phases. When considering the use of BBF in future sleep research there are certain things to consider. First, since brainwaves in REM look similar to the awake state, this could be difficult to replicated as incorporating beta BBF may abruptly awaken the person. Halting BBFs at the end of a 90–110-min sleep cycles to allow for REM may have a better effect than the continual use of delta BBF. If delta BBF is used throughout the entire sleep cycle, it may prohibit the person from entering REM which could negatively impact sleep quality. An example would be REM rebound when BBFs are not in use. This may cause the person to experience an unusual succession of dreams, which may or may not be good for persons with certain mental health issues. Second, age must be taken into consideration when creating a BBF algorithm as increased age may show a decrease in total sleep time and sleep efficiency as well as increase in wake after sleep onset and sleep latency (40). Third, gender should also be considered because although slow wave sleep diminishes as one ages, women typically maintain more slow wave sleep than men (40). Fourth, BBF may be efficacious for different sleep disorders. For example, in the case of insomnia, using alpha and theta to induce sleep and a well-designed BBF algorithm tailored to the listener may be beneficial. As for hypersomnia using the theta-alpha-beta structured waking may mitigate this. For those who have circadian rhythm disorders, due to changing work shifts, change in number of hours available to sleep, or traveling between time zones, the use of a full night audio track that can be adjusted for the number hours available to sleep may help realign the circadian rhythm. Fifth, investigators should be careful when considering using BBF with persons with traumatic brain injury as there is no evidence to support that BBF would be helpful or harmful. Finally, consideration should also be taken when using BBF in persons who suffer from serious tinnitus as the ringing in the ears may make listening to the tones uncomfortable.

### Limitations

The use of polysomnography is the gold standard for assessing sleep. However, when multiple data collection points are needed on an intervention that has not been well-studied, it is best to start by conducting assessments with low participant burden, low risk, low cost, and user-friendly and relevant data collection tools. Using a model hypnogram to construct a BBF algorithm may not work for everyone given that each person has their own sleep cycle rhythm, and that age and gender can play a role. However, if changes are noted in sleep parameters such as sleep latency, wake upon sleep onset, or number of times awakened this may provide evidence that the brainwaves can in fact be entrained. Finally, constructing an audio file that allows breaks for REM is a difficult task as sleep cycles are individualized. Using the 90–110-min mark to halt BBF to provide a break is the best educated option aside from simply using continuous theta BBF for the entire night.

## Conclusion

There are a variety of evidence-based strategies to mitigate poor sleep quality, however BBF is one novel idea, that deserves more research. The use of specialized audio frequencies to affect brainwaves to change the listener state of consciousness has proven efficacious in a variety of circumstances. However, BBFs marketed for sleep often only use one frequency (e.g., theta or delta) which may not allow the listener to transition through the phases of sleep. Phase 1, of this four-phase study, concluded that theta BBF was able to decrease stress to help induce sleep. Phase 2 will now assess if theta and delta BBFs, with breaks to allow for REM, will be able to help sustain sleep. Phase 3 will next incorporate theta, alpha and beta BBFs, respectively at the end of an all-night audio track to trigger a structured waking process with Phase 4 combining lessons learned from Phases 1, 2 and 3 to create a customized all-night audio track to entrain sleep. The data obtained from these feasibility studies will provide information to help construct an all-night audio program with the appropriate BBF and timing to trigger the correct sleep stage for better sleep efficiency. If this concept is feasible, it could be useful for many sleep disorders.

## Ethics statement

This study involving human participants was reviewed and approved by the United States Army Medical Research and Materiel Command Institutional Review Board (#M-10544) and the Regional Health Command-Atlantic Institutional Review Board (#RHCA18010/899685). The participants provided their written informed consent to participate in the study.
